Standard SHCS: CHILD form [37]	To measure behavioural responses to hypnotic suggestions for children aged 6–16 years	- Relaxation/eye closure induction; - 7 test suggestions for time regression, visualisation, ideomotor responses, and post-hypnotic suggestions to re-enter hypnosis at hand clap^a^	0–7: - Low: 0–2; - Medium: 3–5; - High: 6–7	- 0 if absent or negative behavioural response, - 1 if positive behavioural response [37]	20 mins	Just before and during the 1st dressing change	- Moderate correlation with the Stanford Hypnotic Susceptibility, Form A scale: *r* = 0.67 [37] - Established concurrent validity [37]
Modified SHCS: CHILD form [37]	To measure behavioural responses to hypnotic suggestions for children aged 4–8 years	- Active induction in which eyes can be open; - 6 test suggestions for time regression, visualisation, and ideomotor responses	0–6: - Low: 0–1; - Medium: 2–4; - High: 5–6				
Involuntariness numeric scale [39]	To rate involuntariness and automaticity experienced during the responses to SHCS: CHILD suggestions	Age-appropriate question reworded to children’s age regarding experienced involuntariness during responses to SHCS: CHILD items (*did that feel like you made that happen or that it happened by itself?)*^b^	Mean of items scores	Score ranging from 0 (no response), 1 (voluntary response to suggestions) to 5 (involuntary-automatic enactment) for each SHCS: CHILD test item	10 mins	During the 1st dressing change	- Good internal consistency (*α*s: 0.76–0.86) [40] - Adequate construct validity: moderate correlation of involuntariness scores with scores on a standardised hypnotic suggestibility scale (*r* = .49, *p* < .001, 95% *CI* = [.31, .65], *n* = 58) [41]

^a^Anaesthesia suggestion will be incorporated in the ideosensory test suggestion to assess specific responses relevant to hypno-anaesthesia

^b^Following each test suggestion, children will be asked about the involuntariness experienced during responses to test suggestions

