#### Process evaluation

Outcomes of the implementation process are outlined in Table 5. Potential effectiveness will be measured by health-related outcomes of procedural pain, state anxiety, and itch at different time points as guided by the RE-AIM outcome of *effectiveness* (Table 6). The selection of health outcomes measurement tools is based on psychometric properties, feasibility, and clinical utility for children aged from 4 to 16 years (supplementary file 3). Salivary α-amylase, a bio-indicator of the sympathetic adreno-medullary system (produced by norepinephrine-responsive salivary gland cells), will be measured as a stress biomarker. The choice of salivary α-amylase was made as the authors are experienced in administering the test rapidly in children research studies, and based on the measures’ reliability, validity, and sensitivity as a marker of distress and minor stressors [50].

**Table 5 Tab5:** Process evaluation with data collection time-points

Implementation outcome	Measurement	Dressing change time point			Source of data (measurement tool)	Assessor	Dressing change
		Pre	Mid	Post			
Reach	Rate of families willing to participate out of those approached for participation	x			Report	Hypnotherapist	1st dressing change
Acceptability	Parents’ and children’s beliefs/views on hypnotherapy	x			Field notes, semi-structured pre-hypnosis interview^a^		
	Children’s level of perceived self-efficacy	x			1–10 Likert scale		
	Children’s level of positive therapy expectations	x			1–10 Likert scale		
	Satisfaction of parents and children with suggestibility screening, involuntariness measures, and pre-hypnosis interview			x	Satisfaction NRS^b^		
	Satisfaction of parents, children, and clinicians with the hypnotherapeutic session			x	Satisfaction NRS^b^		Each dressing change
	Families’ and clinicians’ likes, dislikes, recommendations, and perceived burden of required time and effort regarding hypnotherapeutic sessions			x	Semi-structured interview^a^ and field notes		Last dressing change
	Satisfaction of families with health outcomes measurements			x	Satisfaction NRS^b^		
Effectiveness	Perceived benefits			x	Field notes, reports of children, parents, and clinicians		
	Safety of hypnotherapy (rate, timing, duration, and severity of adverse events)		x	x			Each dressing change
	Health outcomes	(Refer to Table 6 for details)					

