#### Intervention phase

The hypnotherapist will conduct a semi-structured interview with families following their consent to participate. Saliva samples will be collected immediately before medications at least 20 minutes before removing the burns dressing by placing Salivettes® (Sarstedt Australia Pty Ltd, Mawson Lakes, S.A., Australia) under children’s tongues for 2 minutes. Data on burns characteristics and health outcomes (pre-procedural pain, state anxiety, and heart rate) will be collected at baseline. Hypnotic suggestibility screening will be conducted immediately before the first dressing change to measure behavioural responses to hypnotic suggestions. Children who score low on the hypnotic suggestibility test will be guided to emerge from hypnosis and excluded from the study, whereas those with medium to high scores will receive therapeutic suggestions until the new dressing is applied.

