#### Progression criteria

To proceed with investigating the efficacy of hypnotherapy in children with burns, at least the following criteria should be met: sufficient time to deliver the intervention in > 80% of children who commence hypnotherapy; > 50% of families with moderate to high satisfaction rate; recruitment and study completion rates > 50%; collection of > 50% of data across all time points; hypnotherapist adherence to > 50% of intervention elements in the fidelity checklist with > 50% of children; and the absence of serious side effects. The progression criteria cover components of all of the implementation outcomes (Data Synthesis, page 19, above).

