#### Monitoring

Despite the safety of the intervention, we acknowledge the necessity of protecting children by carefully monitoring them. Adverse events will be monitored by reports from parents, children, and clinicians who review children every few days until wound healing and beyond the time of delivering hypnotherapy. Adverse events will be addressed by the hypnotherapist after each hypnotherapeutic session as specified in the intervention manual and by clinicians using a standardised management protocol of the burns department. The hypnotherapist will also consult with parents to ensure they are comfortable with the experience. The hypnotherapist will discuss children’s follow-up care options with families and provide them with the contact details of hospital personnel to whom they can raise concerns or issues. Investigators will meet weekly to monitor the study’s progress. Following the National Statement on Ethical Conduct in Human Research, events that may influence the safety of participants will be reported to the clinical health service and ethics committee within ten working days and within 48 hours if serious [57].

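### Children hypnotised for suggestibility screening and then excluded as low scorers have no stated place in the adverse event rate or the safety progression criterion

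*Protocol article*

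**What the plan says.** **Screening is intervention, and it is hypnosis.** The Study aims and Intervention sections both list suggestibility screening as a component of the intervention, beside the interview and the hypnotherapeutic session. Table 2 describes it as an induction followed by test suggestions that include time regression, with an anaesthesia suggestion built into the ideosensory item. Its listed duration is 20 minutes.

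**When it happens.** Three descriptions are given:
- Intervention phase: "Hypnotic suggestibility screening will be conducted immediately before the first dressing change". The Hypnotic suggestibility screening text agrees.
- Table 2: "Just before and during the 1st dressing change".
- The opening paragraph of Intervention places it during the first dressing change.

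**Low scorers.** The screening and Intervention phase sections both say that these children are excluded from the study after the test. They continue with standard care.

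**Safety provisions.**
- Table 5, Effectiveness: "Safety of hypnotherapy (rate, timing, duration, and severity of adverse events"), marked Mid and Post, at each dressing change. The Pre cell is blank.
- Monitoring: "Adverse events will be monitored by reports from parents, children, and clinicians who review children every few days until wound healing", and beyond the period of hypnotherapy.
- Monitoring, next sentence: "Adverse events will be addressed by the hypnotherapist after each hypnotherapeutic session as specified in the intervention manual", and also by clinicians under the department's own protocol.
- Progression criteria: one condition for going on to an efficacy study is "the absence of serious side effects". No population is named.

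**The concern.** A safety population should contain everyone exposed to the intervention. Here exposure begins with the screening induction, but a child's place in the study depends on how that induction goes. Children are selected on response after they have been exposed.

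As worded, neither the Table 5 row nor the hypnotherapist's adverse event step reaches a child who leaves after screening. The debriefing of children with negative reactions is likewise listed in Table 3 as part of the hypnotherapeutic session.

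This matters for two reasons. First, the criterion is all-or-nothing: one serious event in a screened-out child reverses it if counted and leaves it met if not. Second, screening has the thinnest safety evidence of the components. The Safety of the intervention section cites nothing on suggestibility screening, the Discussion says the previous burns trial of hypnotherapy did not screen, and the authors describe this study as, to their knowledge, the first to assess the feasibility of screening in paediatric burns.

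**Working it through.** The article states no adverse event rate, safety sample size or error rate, so there is no figure of its own to reproduce. The check is who is reached by each provision, and how many children are affected.

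**1. Reach of each provision, as worded**

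| Provision | Retained child | Child excluded after screening |
|---|---|---|
| Table 5 safety row (Mid, Post) | Yes; event timing is recorded, so a screening event can be reported later in the visit | No study observation stated after exclusion |
| Hypnotherapist's step after each session | Yes | No session takes place |
| Family and clinician reports until healing | Yes | Not stated either way |
| Progression criterion | Yes | Not stated either way |

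**2. Number of children affected**

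Inputs, from Sample size: 30 children receive hypnotherapy; 15% score low.

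- Screened = treated / (1 − share low) = 30 / 0.85 = 35.3, or 36 rounded up.
- Screened out = 35.3 − 30 = 5.3, or 36 − 30 = 6 after rounding up. Hence about 5 to 6.
- Chance that at least one of 36 is a low scorer = 1 − 0.85^36 = 99.7%.
- If the low-score share differs (assumed range): at 10%, 30 / 0.90 = 33.3, so 34 screened and 4 out; at 25%, 30 / 0.75 = 40 screened and 10 out.

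**3. What the extra children add numerically**

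- Exact one-sided 95% upper bound with zero events = 1 − 0.05^(1/n). For n = 30 this is 9.5%; for n = 36 it is 8.0%.
- Chance of seeing at least one event at an assumed true rate of 5% = 1 − 0.95^n. For n = 30 this is 78.5%; for n = 36 it is 84.2%.

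The gain in precision is small. The reason to count these children is that they are the exposed children removed on the basis of their response, and the criterion turns on a single event.

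**The case against.** **Table 5 is not the only safety provision.** The Monitoring section sets wider reporting with no start point that excludes screening. This stands: it would be wrong to say that the protocol collects adverse events only from mid-procedure on.

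**Mid and Post are recording times, not exposure windows.** A reader might infer from the blank Pre cell that all hypnosis before the dressing change goes unobserved. On the stated durations that would be 20/(20+35) = 36% to 20/(20+20) = 50% of the first visit's hypnosis time. The documents do not support this. The safety row records event timing and duration, and satisfaction with the screening is likewise collected at Post. Two of the three timing statements put screening partly or wholly during the dressing change. For retained children, nothing is shown to be lost.

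**Serious events have their own route.** Events that may affect participants' safety go to the health service and ethics committee, within 48 hours if serious, and low scorers have consented and stay in the same clinic's care. This makes it less likely that a serious reaction would go unknown. It does not say that such an event would count against the criterion, and it does not supply the rate of non-serious events.

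**A low score is not poor tolerance.** Correct: the scale counts behavioural responses. The documents do not show that low scorers have more adverse events, so neither the direction nor the size of any bias is established.

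**Defining the safety population can be left to the full protocol or analysis plan.** This is fair as regards the denominator alone. But the exclusion after exposure, the schedule and the progression criterion are all fixed in this article, and a later plan cannot recover events that were not collected.

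**Conclusion.** The concern holds for children excluded after screening. About 5 to 6 of roughly 36 hypnotised children, some 15%, have no stated study safety observation, and the safety criterion can be declared met without them. A safety conclusion about screening plus hypnotherapy would then rest only on children kept for therapy.

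This rests on three assumptions: that 30 is the number treated, that the article's 15% low-score rate is right, and that exclusion from the study ends study data collection, which the text implies but does not spell out. The general monitoring might be meant to cover these children; if so, the article needs to say so.

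The conclusion does not extend to screening events in retained children, and it is not a finding that the adverse event rate will be too low. It is a moderate defect, almost certain to arise and easy to correct.

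**What to change.** 1. State that adverse events are recorded for every child who starts the screening induction, and take the report from low scorers before they leave the visit.
2. Name all children who started the induction as the denominator for the adverse event rate and as the population for the safety progression criterion. Report retained and screened-out children separately as well as together.
3. Align the Table 5 safety row with the Monitoring section, so that the first visit visibly covers screening, and extend the wording tied to hypnotherapeutic sessions so that recording after screening is included.
4. Reconcile the three statements of when screening takes place (Intervention; Hypnotic suggestibility screening and Intervention phase; Table 2).

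The cost is a table edit, a few sentences, and one brief question to about 5 to 6 families who have already consented. No extra staff are needed.

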### Data analysis and interpretation

Qualitative and quantitative data will be collected concurrently and subsequently analysed independently before integration.

#### Quantitative analysis

Descriptive statistics (frequencies, percentages, medians, and interquartile ranks) will be used to present data on children’s sociodemographic and clinical characteristics as well as process evaluation and health outcomes data. Suggestibility screening data will be stratified by age corresponding to the age groups of the two different forms of the Stanford Hypnotic Scale for Children that will be used in the study (4 to 6 years and 6 to 16 years). Data analysis will be conducted using Excel and SPSS 26 (IBM Corporation, Armonk, NY, USA).

#### Qualitative analysis and interpretation

Semi-structured interviews will be audio-recorded, transcribed verbatim, and analysed using framework analysis involving transcription, familiarisation, coding, developing a working thematic framework, charting of data into the framework, and interpretation of data [56]. Following familiarisation and coding of several interviews, qualitative data will be summarised by category and charted individually to a Microsoft Excel spreadsheet matrix to form a working framework [56]. After systematically indexing subsequent transcripts using the generated codes and categories of the framework, data will be interpreted within-and-between groups (children, parents, clinicians) to reach a consensus on themes. Themes will be generated using an inductive approach. Following the completion of the inductive coding, interview data will be mapped to the Theoretical Framework of Acceptability deductively [27]. The credibility of the analysis will be maximised using member checking, independent coding by two researchers, triangulation of the results across participant groups (e.g. parents and children), and reflexivity. Reflexivity involves keeping notes of what occurs during the interview (field notes), early data interpretations, as well as ideas and impressions by researchers conducting the interviews and analysing the data [56]. Within-group triangulation of interview data will be conducted using emergent themes to identify differences according to child, parent, or clinician report [26]. The strength of convergence will be assessed based on the frequency and range of overlapping themes. Themes will be rated across participant reporting groups to identify those with the highest versus the minimum convergence. Differences in evidence across the groups will be reported.

### Data synthesis

A transformative approach to data synthesis will be adopted to integrate different sources and types (qualitative and quantitative) of evidence through triangulation and interpretation based on the implementation outcomes [28]. For instance, acceptability will be assessed using interview data as well as ratings of families and clinicians’ satisfaction, children’s self-efficacy, and positive therapy expectations. Some qualitative data will be merged into quantitative counts. For instance, the number of times recurrent themes related to acceptability emerge in interviews will be counted. Following the triangulation of data, each implementation outcome will be allocated a score (1 = less successful, 2 = moderately successful, 3 = highly successful) based on the availability of data addressing the implementation outcome and the positivity of outcome measures (supplementary file 4).

### Procedures

#### Recruitment

Children presenting to the specialist burns centre for their first burns dressing change and their parents will be screened for eligibility after consulting with clinicians regarding children’s potential eligibility. It is anticipated that approximately three children per week will be recruited (total recruitment period 15 weeks).

#### Intervention phase

The hypnotherapist will conduct a semi-structured interview with families following their consent to participate. Saliva samples will be collected immediately before medications at least 20 minutes before removing the burns dressing by placing Salivettes® (Sarstedt Australia Pty Ltd, Mawson Lakes, S.A., Australia) under children’s tongues for 2 minutes. Data on burns characteristics and health outcomes (pre-procedural pain, state anxiety, and heart rate) will be collected at baseline. Hypnotic suggestibility screening will be conducted immediately before the first dressing change to measure behavioural responses to hypnotic suggestions. Children who score low on the hypnotic suggestibility test will be guided to emerge from hypnosis and excluded from the study, whereas those with medium to high scores will receive therapeutic suggestions until the new dressing is applied.

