### Study aims and objectives

The primary aims are to investigate the feasibility and acceptability of the intervention (i.e. pre-hypnosis interview, hypnotic suggestibility screening, and hypnotherapeutic session) and evaluation procedures (i.e. recruitment and health outcome data collection). Additionally, the reach, adoption, potential effectiveness, and implementation (i.e. fidelity) of the intervention and evaluation procedures will be examined as secondary outcomes.

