##### Hypnotic suggestibility screening

Hypnotic suggestibility, an important factor in response to hypnotic suggestions, will be screened for using the Stanford Hypnotic Scale for Children (SHCS-Children) immediately before children’s first dressing change (Table 2) [37]. Individuals with low hypnotic suggestibility are unlikely to benefit from hypnotherapy whereas those with high suggestibility show the strongest response to hypnotic analgesia and those with medium suggestibility have been shown to obtain pain relief [9, 38]. Therefore, only children with medium to high hypnotic suggestibility scores will be eligible for hypnotherapy to limit participant-related confounding factors by having more homogenous participants in terms of response, potentially increasing the effects of hypnotherapy. Children with low hypnotic suggestibility scores will be excluded from the study but will continue to receive standard care to avoid exposing children who are unlikely to obtain pain relief with hypnotherapy to an unnecessary burden of hypnosis (Table 2). Low scores (below three on the standard SHCS-Children and below two on the modified SHCS-Children) were determined based on the hypnotic suggestibility literature (Table 2). Due to the great variability in response to specific suggestions, individuals with high hypnotic suggestibility may be highly responsive to some suggestions and unresponsive to others [33]. Therefore, a tailored version of the hypnotic suggestibility  scale incorporating anaesthesia suggestions will be used to assess specific responses to hypno-anaesthesia suggestions and thus inform the delivery of therapeutic suggestions [33]. Responses to test suggestions of the hypnotic suggestibility scale will be used to guide the hypnotherapeutic session by informing the hypnotherapist on children’s preferences (i.e. favourite music type and memory) and the type(s) of suggestions they are responsive to [33].

**Table 2 Tab2:** Description and psychometric properties of measures of behavioural and involuntariness responses to hypnotic suggestions

Measurement	Goal	Description	Score ranges	Scoring	Duration	Time point	Psychometric properties

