Adoption	Rate of clinicians consenting to participate among those conducting dressing changes.	x			Report	Hypnotherapist	1st dressing change
Implementation: fidelity	Retention rate		x	x	Report on the rate of children completing the intervention		Each dressing change
	Fidelity in collecting data on health outcomes			x	Response rate in data collection forms (amount and type of missing data)		
	Fidelity in delivering the intervention			x	Study-specific checklist^c^	Independent observer expert in clinical hypnosis	
	Additional adaptations and modifications			x	Documentation of what, when, and how adaptations occurred		
Feasibility	- Adequacy of resources (adequately working music player, calm space) - Presence/absence of interruption (s) - Time availability (sufficient for delivering study procedures) [31]	x	x	x	- Field notes - Intervention pre-recording	Hypnotherapist	

^a^Following permission from children and parents to audiotape the intervention

^b^Adult participants (parents or clinicians) and children ≥ 8years will self-report their satisfaction; proxy reports will be obtained from parents for children < 8years

^c^An independent assessor (preferably hypnotherapist) will assess the fidelity of delivering the intervention through analysing pre-recordings using a study-specific checklist based on the intervention manual; % of core elements and non-core elements delivered will be reported

**Table 6 Tab6:** Health-related outcomes measured using the RE-AIM outcome of effectiveness with data collection time points

RE-AIM outcome	Health-related outcomes		Dressing change time point			Source of data (measurement tool)	Assessor	Dressing change
			Pre	Mid	Post			
Potential effectiveness	Acute procedural pain	Pain intensity	x	x retro	x	FPS-R (≤ 8 years) [51], I-INRS (≥ 8 years) [52], FLACC^a^ [53]	Hypnotherapist	Each dressing change
		Pain unpleasantness				UNRS (≥ 8 years) [52]		
	State anxiety		x	x retro	x	VAS [54]		
	Itch	Intensity			x	Itch-NRS: self-report ≥ 8 years, proxy-report < 8 years [55]		From 3rd dressing change
		Frequency				Questions on itch episodes (per week, per day) [55]		
	Physiologic measures of pain and distress	Heart rate	x	x	x	Monitoring device		Each dressing change
		Salivary α amylase (in children’s saliva samples)	x		x	ELISA kits (Stratech Scientific, Avalon NSW)	Independent observer	

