### Study strengths and limitations

The study will enhance knowledge about the safety of hypnotherapy by assessing the severity, timing, and duration of adverse events. The study is to our knowledge the first to assess the feasibility of hypnotic suggestibility screening in paediatric burns. Screening participants for hypnotic suggestibility may reduce participant-related confounding factors, prevent exposing children to an unnecessary burden of hypnosis, and increase hypnotherapy effects by excluding those who are unlikely to obtain pain relief with hypnotherapy. Plus, the use of an innovative mixed-methods design integrating multiple sources and data collection methods as informed by implementation frameworks can assist in identifying common barriers to implementation across settings. Yet, the success (or otherwise) of implementing the hypnotherapy intervention and evaluation procedures may be related to the local context and may not generalise to other settings. The generalisability of the study may also be limited by the exclusion of patients who require general anaesthesia for their first dressing change in the operating room and those with low hypnotic suggestibility as well as the small sample size. Excluding children with low hypnotic suggestibility scores may also lead to selection bias but is unlikely to hinder the interpretation of results considering the small rate of low suggestibility in the population (15%).

Other limitations include the lack of a control group and validation of pain unpleasantness numeric rating scale in younger children, although no other measures are available for this age group [52]. The Stanford Hypnotic Scale for Children used to measure hypnotic suggestibility is limited by the lack of validity testing with Australian children and the lack of psychometric data except that obtained during the scale development [62]. Yet, in the absence of other brief scales validated for children, the scale will be used due to the short length and adaptability to children’s preferences and age.

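### Families of low-scoring children leave the study before the only satisfaction rating of the interview and screening, so that part of the primary acceptability aim is rated only by families whose child passed

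*Protocol article*

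**What the plan says.** All references are to the protocol article.

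- **Study aims and objectives** makes feasibility and acceptability of the intervention primary, and lists the intervention as "pre-hypnosis interview, hypnotic suggestibility screening, and hypnotherapeutic session".
- **Procedures, Intervention phase** fixes the timing: "Hypnotic suggestibility screening will be conducted immediately before the first dressing change to measure behavioural responses to hypnotic suggestions". It continues: "Children who score low on the hypnotic suggestibility test will be guided to emerge from hypnosis and excluded from the study".
- **Hypnotic suggestibility screening** repeats the rule: "Children with low hypnotic suggestibility scores will be excluded from the study but will continue to receive standard care".
- **Process evaluation, Table 5** has one row that rates these components: "Satisfaction of parents and children with suggestibility screening, involuntariness measures, and pre-hypnosis interview". It is marked Post, at the 1st dressing change. The semi-structured interview on likes, dislikes and burden is at the last dressing change and concerns the hypnotherapeutic sessions.
- **Table 4** marks sociodemographic data Post and burn characteristics Pre, both at the 1st dressing change.
- **Progression criteria** requires more than 50% of families to have moderate to high satisfaction, without saying with what.
- **Study strengths and limitations** acknowledges the exclusion: "Excluding children with low hypnotic suggestibility scores may also lead to selection bias but is unlikely to hinder the interpretation". The reason given is that low suggestibility is uncommon (15%).

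**The concern.** A family whose child scores low has been through both components under evaluation: the interview, and a screening that Table 2 puts at 20 minutes. They then receive no hypnotherapy. Their view of whether the screening was worthwhile, too long or upsetting is part of what acceptability of screening means, and they leave because of the screening result. Satisfaction among the remaining families is conditional on a good result from the procedure being rated.

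The article describes the study as the first it knows of to assess such screening in paediatric burns, and expects it to guide future use of suggestibility tools. Any later trial that screens will also have low scorers. The limitation paragraph rests on the 15% rate and does not take up the aim of evaluating the screening itself.

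**Working it through.** **1. Order of events**

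| Step | When | Low scorers included? |
|---|---|---|
| Beliefs, self-efficacy, therapy expectations (Table 5) | Pre | Yes, by timing |
| Burn characteristics, baseline pain, anxiety, heart rate (Table 4; Intervention phase) | Pre | Yes, by timing |
| Feasibility notes on resources, interruptions, time (Table 5) | Pre, Mid, Post | Pre part, by timing |
| Suggestibility scores | Just before and during the 1st dressing change (Table 2) | Yes, by timing |
| **Low scorers leave the study** | At screening | |
| Satisfaction with screening, involuntariness measures and interview (Table 5) | Post, 1st dressing change | No |
| Sociodemographic data (Table 4) | Post, 1st dressing change | No, as scheduled |

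The Abstract plans for up to 30 parents, the same number as the children to be treated. That leaves no room for parents of additional low scorers.

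**2. How many families**

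Inputs from Sample size: at least 5 potentially eligible children a week, 15 weeks, 15% non-participation, 15% low suggestibility, 30 children to receive hypnotherapy.

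- Plan's own figure: 5 × 15 = 75, and 75 × 0.85 × 0.85 = 54.2. The stated minimum of 30 is met as a lower bound but not reproduced as a point figure. The present point does not depend on it.
- Screened for 30 treated: 30/0.85 = 35.3, so 35 to 36.
- Unrated: 35.3 − 30 = 5.3, so 5 to 6 families.

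**3. What the missing ratings could do to a threshold of more than 50%**

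This assumes one child per family, ratings from all 30 passers, and a criterion based on screening ratings. Let *s* be the number satisfied among the 30. With 36 screened and 6 unrated, the result over all screened lies between *s*/36 (no low-scoring family satisfied) and (*s* + 6)/36 (all satisfied). No satisfaction rate has to be assumed.

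| *s*/30 observed | Lowest, *s*/36 | Highest, (*s* + 6)/36 |
|---|---|---|
| 16 (53%) | 44% | 61% |
| 18 (60%) | 50% | 67% |
| 19 (63%) | 53% | 69% |
| 24 (80%) | 67% | 83% |
| 27 (90%) | 75% | 92% |

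The criterion is certain to hold only if *s* > 36/2 = 18, that is from 19/30 (63%). With 35 screened and 5 unrated, *s* must exceed 17.5, so 18/30 (60%).

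**4. If the low rate is not 15%** (assumed range 10% to 30%)

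- 10%: 30/0.90 = 33.3, so 34 screened and 4 unrated; safe from 18/30 (60%).
- 30%: 30/0.70 = 42.9, so 43 screened and 13 unrated; safe from 22/30 (73%).

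**The case against.** Several points on the other side are sound.

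- **Feasibility.** A reader might infer that feasibility of the screening is also seen only in passers. The documents do not support that. Pre notes on time, interruptions and resources, and the suggestibility scores, arise before anyone leaves, and Quantitative analysis plans to report screening data by age group with no restriction to passers.
- **Describing low scorers.** A reader might infer that they cannot be described. Burn characteristics and baseline measures precede screening, and charts and medical records are also named as sources. Only the sociodemographic row is scheduled after exclusion.
- **The final interview.** Its absence costs nothing here, since it concerns sessions that low scorers never had.
- **The progression criterion.** It may refer to satisfaction with the sessions, which suits its stated purpose of moving on to efficacy. Low scorers would then not belong in its denominator.
- **Direction.** Nothing in the article shows that low-scoring families are less satisfied.
- **Whether they really go unrated.** The Table 5 row does not limit who rates, and Figure 1 and the supplementary files are not shown. Yet the exclusion is stated twice without qualification, and the reason given for it, sparing children unnecessary hypnosis, does not require dropping a rating form.

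These points narrow the concern to post-screening satisfaction and the sociodemographic row. They do not remove it.

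**Conclusion.** The point holds for acceptability. As written, satisfaction with the interview and the screening, both inside the primary aim, is observed only where the child passed. About 5 to 6 of 35 to 36 screened families are unrated at the protocol's 15% rate. An upward bias is plausible but not demonstrated, so it should not be stated as fact.

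A reader might also infer that the progression decision is compromised. That follows only if the criterion uses screening ratings, which the text does not specify, and only if satisfaction among passers is below about 63%. At 27/30 the result over all screened would still be at least 75%. Even then the screening estimate describes a selected group, and the limitation paragraph does not answer that.

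Measures taken before exclusion are not lost by timing, but the article does not say that they are kept once a child is excluded. Ratings not collected at the visit cannot be recovered by later analysis, so this should be settled before enrolment.

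**What to change.** 1. In both places that remove low scorers from the study (Hypnotic suggestibility screening; Intervention phase), state instead that they do not receive hypnotherapy but remain in the screening evaluation set.
2. At the same visit, collect from these families the existing Table 5 satisfaction rating for the screening and interview, and the Table 4 sociodemographic data. Let the planned number of parents cover all screened families.
3. State that data gathered before exclusion are kept.
4. Report screening and interview outcomes over all screened children, and hypnotherapy outcomes over those who commence it.
5. In Progression criteria, name the satisfaction rating and the denominator.

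The cost is protocol wording, a sentence in the consent material and about six short forms, with no extra visit. Only data collection changes, not who receives hypnotherapy.
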